In order to measure the impact of the first episode of ARI or SARI on functional status, we will conduct a nested case-control study of participants recovering from an ARI or SARI. Participants who experience their first ARI or SARI after enrollment will be matched with cohort participants who have not yet experienced an ARI or SARI based on age ( $\pm 5$  years), sex, influenza vaccination and most recent functional status measurement. Interviews will be conducted three to four weeks after the onset of ARI or SARI in the case and both cases and controls will be compared with respect to changes in functional status measurement (VES-13 score  $\geq 3$ ).

Elderly with COPD: In the standardized baseline questionnaire assessing functional status and medical conditions, participants will be asked whether they have been diagnosed with COPD. If they do, at the end of two years, the number of outpatient visits and inpatient admissions for exacerbations of COPD will be determined (by directly observing their medical records). A COPD exacerbation is defined as “a sustained worsening of the patient's condition, from the stable state and beyond normal day-to-day variations that is acute in onset and may warrant additional treatment in a patient with underlying COPD” (11). We will use the collected nasal self-swabs or healthcare worker collected nasopharyngeal swab taken when the participant was experiencing an ARI or SARI to confirm whether the COPD exacerbations the participant experienced were influenza-associated. At the end of the study, the incidence of all-cause COPD exacerbations and laboratory confirmed influenza-associated COPD exacerbations among the elderly with COPD who fit the ARI or SARI case definitions will be calculated. The incidence among those who were vaccinated will be compared to those who were not vaccinated.

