All persons with COPD are required to report to the district hospital's COPD clinic if they are experiencing exacerbations and for check-up. If a participant has COPD, the participant's medical records will be checked by a research nurse at each district hospital to record when and the number of times the participant visited a health center to seek care for a COPD exacerbation onto an electronic questionnaire CRF. We will know if the COPD exacerbation was laboratory-confirmed influenza-associated through results of the nasopharyngeal swab testing during their COPD clinic appointment at the same time period and whether patient was experiencing an ARI or SARI.

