To estimate the incidence of influenza-associated COPD exacerbations among elderly with COPD, we will calculate the total number of laboratory-confirmed influenza-associated COPD exacerbations per total number of COPD patients within our cohort over a year (primary objective 1.3). We will compare the incidence among those that were vaccinated with IIV3 versus those that were not vaccinated with IIV3. In order to account for correlation among repetitive measurements from each individual, we will also employ GEE methodology. This method will also allow us to adjust for underlying confounders such as smoking history and age.

Blood samples will be taken from a select number of participants who will have had IIV3 to test the antibody response of IIV3 among the elderly (objective 2.2). These blood samples will be taken at baseline before receiving the shot, and then again after 28 days (1 month), 180 days (6 months), and 360 days (12 months) later. The blood samples will be tested for HI antibodies. Everyone with a baseline HI assay  $\geq 10$  who has a four-fold increase in HI antibody count post vaccination or who has a baseline HI assay  $< 10$  who has a post vaccination count  $\geq 40$  will be considered seroconverted against influenza. One additional blood draw will be taken after 28 days of subsequent vaccination in the second year to compare the effect of prior vaccination on level of immunological response. We will use a random effects model (RE) to compare blood

samples at the post vaccination dates to the baseline HI assay to determine how long participants vaccinated with IIV3 retain an adequate number of HI antibodies. RE allows us to control for the differences in antibody count amongst all individuals across unequal intervals and obtain a mean distribution. This methodology will also allow us to control for confounders such as age and factors which make participants immuno-compromised.

We will also evaluate a simpler outcome, the incidence rate of RSV among elderly with ARI or SARI over the entire observation period (second-objective 2.3), which should be similar between those that were vaccinated with Influenza IIV3 and those that were not.

Aggregate results may be shared with relevant CDC programs in which the findings of this study may have immediate policy implications. Opportunities for publication will be sought.

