## **Limitations**

The main limitation of this study is its limited generalizability to Thailand. While we are able to obtain a representative sample of Nakhon Phanom Province, the people in NP may be different than people from other parts of Thailand. Another limitation is sampling bias. The study's sample may be biased since healthier people are usually more willing to participate in studies compared to people who are more ill, which would not represent the target population of all types of elderly people. In order to diminish the potential of sampling bias, our inclusion criterion includes all elderly despite illness type.

It is possible that not all respiratory events in the enrolled elderly will be captured, due to inability to communicate, misunderstanding and even memory loss. To a large extent, a lot of the success for this project may rely on the relationship between the household and health volunteer and role of the caregiver for participants greater than 80 years of age. Another limitation to our study is that baseline enrollment data and weekly follow-up data is relying heavily on self-report. It is possible for participants to be unaware of whether they have certain underlying co-

morbidities if they do not regularly visit the physician, it is possible for them to under or overestimate their functional status, and it is possible for them to forget to take a nasal self-swab or remember that they even experienced an ARI or SARI. In order to mitigate these potential issues, we are using a reliable and sensitive functional status questionnaire and following-up with participants weekly in case they forget to call us.

Although Thailand provides free vaccinations for elderly, there are not enough purchased to vaccinate all elderly in Thailand. Due to the limited number of vaccines, elderly that are sicker and see health care professionals more often are more likely to become vaccinated than those who are healthier. The elderly who join our immunogenicity study will most likely be sicker than the general population and are more likely to be immunocompromised. Because of this selection bias, our immunogenicity study will most likely show a lower rate of seroprotection among the elderly than what is actually representative of the average elderly population.

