| We are almost finished with the questionnaire. We would like to ask you a few questions about your economic and personal situation. |                                                                                   |                                                                                                                       |  |
| 54                                                                                                                                         | Sex                                                                               | 1 Male
2 Female                                                                                                    |  |
| 55                                                                                                                                         | Are you currently married?                                                        | 1 Married
2 Widowed
3 Divorced/separated
4 Single (never married)
77 Do not know
99 Declined to answer |  |
|                                                                                                                                            |                                                                                   |                                                                                                                       |  |
| 56                                                                                                                                         | How many other people live with you in this house?                                | _____
77 Incomplete data
99 Declined to answer                                                                  |  |
| 57                                                                                                                                         | If you become ill, where do you normally seek care? Check only one answer. | 1 District hospital
Specify: _____
2 Provincial hospital
Specify: _____                                      |  |

|    |                                                                                   |                                                                                                                                                                                                                  |                           |

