|----|-----------------------------------------------------------------------------------|------------------------------------------------------------------------------------------------------------------------------------------------------------------------------------------------------------------|---------------------------|
|    |                                                                                   | 3 Sub-district health center
Specify: _____
4 Private physician
5 Don't seek care/drug store
6 Other
77 Do not know
99 Declined to answer                                                      |                           |
| 58 | What is the highest level of education you completed?                             | 0 Never attended school
1 Some primary
2 Completed primary
3 Some secondary
4 Completed secondary
5 Some post-secondary education
6 Graduate degree
77 Do not know
99 Declined to answer |                           |
| 59 | Are you the head of your household?                                               | 1 Yes
2 No
77 Do not know
99 Declined to answer                                                                                                                                                         | If yes, skip to 61 |
| 60 | If no, what is the highest level of education completed by the head of household? | 0 Never attended school                                                                                                                                                                                          |                           |

|                                                                                                        |                                                             |                                                                                                                                                                                       |                          |
|--------------------------------------------------------------------------------------------------------|-------------------------------------------------------------|---------------------------------------------------------------------------------------------------------------------------------------------------------------------------------------|--------------------------|

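### Objective 1.3 counts COPD exacerbations from records checked at the district hospitals but divides by all participants with COPD, so incidence may be understated and VE is at risk of bias if capture differs by vaccination status

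*Protocol*

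**What the plan says.** **Numerator.** Protocol section 3.1.4 takes the number of outpatient visits and admissions for exacerbations from medical records at the end of two years. Section 7.5.1 gives the procedure: "medical records will be checked by a research nurse at each district hospital to record when and the number of times the participant visited". What is counted there is care sought for an exacerbation at a health center. The reason offered is that "All persons with COPD are required to report to the district hospital's COPD clinic if they are experiencing exacerbations and for check-up".

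**Denominator.** Section 7.9 divides by the total number of COPD patients in the cohort. COPD status comes from the baseline interview (form 4b, items 33 and 34, which ask about physician-diagnosed conditions), not from registration at the district COPD clinic.

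**Usual source of care.** Item 57 of form 4b asks "If you become ill, where do you normally seek care". Besides the district hospital and the sub-district health center, the codes include the provincial hospital, "4 Private physician", and a code for those who seek no care or use a drug store. For the cost objective (1.2), section 7.5.1 plans for private-clinic visits and over-the-counter treatment by questionnaire. Objective 1.3 has no such supplement.

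**Adjustment and limitations.** For objective 1.3, section 7.9 says that the GEE model can "adjust for underlying confounders such as smoking history and age". The Limitations section says that "elderly that are sicker and see health care professionals more often are more likely to become vaccinated". It does not mention exacerbations treated outside the reviewed records.

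**The concern.** A participant who takes an exacerbation to a private physician, a drug store or nobody stays in the denominator but may add nothing to the numerator. Attendance at the district COPD clinic is stated as a requirement; no step verifies it. The first consequence is that incidence, which is itself part of objective 1.3, may be too low.

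The second concerns VE. If the chance that an exacerbation is recorded rises with contact with public health services, and the chance of vaccination rises with it too, recording will be more complete among the vaccinated. Their rate is then understated less, and VE for all-cause and influenza-associated exacerbations moves towards zero or below. This would happen even if both groups had the same true exacerbation rate, and adjustment for smoking and age does not remove it. A null result on a primary objective could then not be told apart from unequal recording.

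**Working it through.** The protocol states no sample size, rate or capture share for objective 1.3, so there is no figure of its own to reproduce. The check is the algebra of capture, with assumed shares.

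**1. Effect of capture on VE.** Let s_v and s_u be the shares of exacerbations recorded in vaccinated and unvaccinated participants. Then observed VE = 1 − (1 − true VE) × s_v / s_u. The true VE of 40% is borrowed from the cohort sample size in section 7.1.5, for illustration.

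| s_v | s_u | Observed VE, true 40% | Observed VE, true 0 |
|---|---|---|---|
| 0.8 | 0.8 | 40% | 0 |
| 0.6 | 0.6 | 40% | 0 |
| 0.9 | 0.8 | 1 − 0.6 × 1.125 = 32.5% | −12.5% |
| 0.9 | 0.7 | 1 − 0.6 × 1.286 = 22.9% | −28.6% |
| 0.9 | 0.6 | 1 − 0.6 × 1.5 = 10% | −50% |
| 0.7 | 0.9 | 1 − 0.6 × 0.778 = 53.3% | 22.2% |

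Equal under-capture leaves the ratio alone, and the reverse pattern raises VE. A capture ratio of 1 / 0.6 = 1.67 would erase a true VE of 40%.

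**2. The same effect through usual source of care.** Assume that 90% of exacerbations are recorded for users of reviewed facilities and a share d for others, who make up p_v of the vaccinated and p_u of the unvaccinated. The rate ratio is multiplied by [(1 − p_v) × 0.9 + p_v × d] / [(1 − p_u) × 0.9 + p_u × d].

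- p_v = 10%, p_u = 25%: d = 0 gives 0.810 / 0.675 = 1.200; d = 0.3 gives 0.840 / 0.750 = 1.120; d = 0.5 gives 0.860 / 0.800 = 1.075. A true VE of 40% reads 28.0%, 32.8% and 35.5%.
- p_v = 5%, p_u = 15%: the multipliers are 0.855 / 0.765 = 1.118, 0.870 / 0.810 = 1.074 and 0.880 / 0.840 = 1.048. VE reads 32.9%, 35.6% and 37.1%.

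If capture depends only on usual source of care, s_v / s_u is 1 within each stratum where anything is recorded. Under that assumption, conditioning on item 57 removes the bias. With d = 0 the stratum of other users has no recorded events, and only the restricted analysis is informative.

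**3. Size of the subgroup.** The only prevalence given is 7.11%, for elderly people around Bangkok in 2002 (section 4.2); applying it here is an assumption. It gives 0.0711 × 2,724 = 194 to 0.0711 × 3,133 = 223 participants. With half vaccinated and the section 7.1.5 rates (6% unvaccinated; 6% × 0.6 = 3.6% vaccinated), two years yield:

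- n = 194: 97 × 0.06 × 2 = 11.6 and 97 × 0.036 × 2 = 7.0 influenza events, about 19;
- n = 223: 111.5 × 0.06 × 2 = 13.4 and 111.5 × 0.036 × 2 = 8.0, about 21.

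The 95% limits on the rate ratio lie a factor exp(1.96 × √(1/a + 1/b)) either side, where a and b are the two counts: about 2.6 and 2.4. This does not describe the all-cause outcome, for which no rate is given.

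**The case against.** The strongest reply is that the protocol shows a possible gap, not a bias. Several parts of it stand.

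- A reader might infer from form 4b that COPD patients are expected to go elsewhere. The form does not say so: item 57 lists answers about illness in general, put to everyone, and section 7.5.1 says that COPD patients must attend the district clinic. Nothing shows that they do not.
- A reader might also infer that item 57 goes unused. That cannot be established. The covariates in section 7.9 are given as examples, distance to a health facility is named for the main VE model, propensity modeling is planned in section 3.1.1, and a SAP may name the item.
- The Limitations sentence concerns being sicker and how often professionals are seen, not which facility is used. People who use private physicians also see professionals, and the mobile vaccination clinics in section 7.6 may loosen the link between vaccination and facility care.
- Virology does not depend on the clinic alone. Section 3.1.4 accepts home self-swabs, and weekly contacts look for worsening chronic cough wherever care is sought. But section 3.1.4 still takes the exacerbation itself from medical records, and swabs do not help the all-cause count.
- The reach of the record review is unclear. Section 3.1.4 sets no facility limit and section 7.5.1 speaks of visits to a health center, so sub-district visits may be included.
- For influenza-associated exacerbations, random error under the assumptions above (a factor of about 2.4 to 2.6) far exceeds multipliers of 1.05 to 1.20.

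These points remove any claim of demonstrated bias or known size. They do not touch the mismatch between where exacerbations are counted and who is in the denominator. The protocol fixes that mismatch, so it is more than a covariate detail left to a SAP.

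**Conclusion.** The point holds as a risk. Incidence of exacerbations may be understated, because some may be treated where the reviewed records do not reach. VE is at risk of bias only if capture differs by vaccination status after adjustment. The protocol's own remark on contact with professionals and vaccination makes bias towards the null the likelier direction, but does not settle it.

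The size cannot be computed from the documents. Under the assumed usual-source shares, a true VE of 40% would read 28% to 37%; with other assumed capture shares it could fall further or rise. The reading that the comparison is already known to carry detection bias is not supported: it would need evidence of unequal capture, and the protocol gives none. Because this is a primary objective and the relevant variable is already collected, the plan should address it.

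**What to change.** In section 7.9, for objective 1.3:

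1. Name usual source of care (form 4b, item 57) as a covariate in the GEE model, grouped by whether the facility's records are reviewed.
2. State which facilities' records are reviewed, and in particular whether sub-district health centers are included; use the same definition for the grouping.
3. Add a sensitivity analysis restricted to participants whose usual source of care is one of those facilities.
4. Describe the outcome as exacerbations recorded at those facilities, and add possible incomplete capture to the Limitations.

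The covariate can correct only in part, since item 57 is a single baseline answer about illness in general. The restricted analysis and the accurate label do more.

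The cost is wording, one more parameter in a small subgroup, and one more model. With half vaccinated, the restricted analysis would lose 0.5 × 10% + 0.5 × 25% = 17.5% of COPD participants under the first set of assumed shares (34 to 39 of 194 to 223) and 0.5 × 5% + 0.5 × 15% = 10% under the second (19 to 22). No new data collection is needed.

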**End of Questionnaire**

**4c. Weekly Contact Questionnaire (For Health Volunteer)**

|                                                                                                                                                                                               |                                                                                                                                                                                       |
|-----------------------------------------------------------------------------------------------------------------------------------------------------------------------------------------------|---------------------------------------------------------------------------------------------------------------------------------------------------------------------------------------|
| Study identification number                                                                                                                                                                   |                                                                                                                                                                                       |
| Caller's name                                                                                                                                                                                 |                                                                                                                                                                                       |
| Type of Weekly contact                                                                                                                                                                        | Please choose:    In Person        Phone                                                                                                                                              |
| Week of follow-up                                                                                                                                                                             |                                                                                                                                                                                       |
| Date                                                                                                                                                                                          | (DD/MM/YY)                                                                                                                                                                            |
| Results                                                                                                                                                                                       | 1 Declined (wishes to discontinue with the study)

Specify reason:

2 Unable to contact (this is the ____ consecutive time)

3 Contact made and interview completed |
| (On phone or in person) Hello, my name is _____ and I am a study team member from the Ministry of Public Health. May I please speak to _____(participant or caregiver of participant)? |                                                                                                                                                                                       |
| [If not a home] When would be a good time to call back to speak to him/her?

_____                                                                                               |                                                                                                                                                                                       |

| No                                                                                                                                                                         | Questions and filters (variable names)                  | Coding categories                       | Skip |
|----------------------------------------------------------------------------------------------------------------------------------------------------------------------------|---------------------------------------------------------|-----------------------------------------|------|
| .                                                                                                                                                                          |                                                         |                                         |      |
| If the participant has been sick and took nasal self-swabs or had a nasopharyngeal swab taken recently, ask the following questions. Otherwise, skip to question 3. |                                                         |                                         |      |
| 1                                                                                                                                                                          | Have you recovered from your acute respiratory illness? | 1 Yes

2 No

77 Do not know |      |

|                                                                                                                                                                                                                             |                                                                        |                                                                                                                        |                                            |
|-----------------------------------------------------------------------------------------------------------------------------------------------------------------------------------------------------------------------------|------------------------------------------------------------------------|------------------------------------------------------------------------------------------------------------------------|--------------------------------------------|
| 2                                                                                                                                                                                                                           | How many days ago did you recover from your acute respiratory illness? | 1 Today
2 Yesterday
3 2 days ago
4 3 days ago
5 4 days ago
6 5 days ago
7 6 days ago
8 7 days ago |                                            |
| Mark calendar/appointment sheet to call participant 1 week after they say they recovered from their respiratory illness to take the Functional Status Questionnaire and the Outcomes and Costs of ARI Questionnaire. |                                                                        |                                                                                                                        |                                            |
| 3                                                                                                                                                                                                                           | In the last week, have you been sick with a new, acute illness?        | 1 Yes
2 No
77 Do not know                                                                                        | If no, skip to end of questionnaire |
| In the last week, have you had a NEW:                                                                                                                                                                                       |                                                                        |                                                                                                                        |                                            |
| 4                                                                                                                                                                                                                           | Cough, or a worsening of a chronic cough?                              | 1 Yes
2 No
77 Do not know                                                                                        |                                            |
| 5                                                                                                                                                                                                                           | Fever?                                                                 | 1 Yes
2 No
77 Do not know                                                                                        |                                            |
| 6                                                                                                                                                                                                                           | Nasal discharge/congestion?                                            | 1 Yes
2 No                                                                                                          |                                            |

|                                                                                                                                                                                                                                              |                                                          |                                 |  |
|----------------------------------------------------------------------------------------------------------------------------------------------------------------------------------------------------------------------------------------------|----------------------------------------------------------|---------------------------------|--|
|                                                                                                                                                                                                                                              |                                                          | 77 Do not know                  |  |
| 7                                                                                                                                                                                                                                            | Sore throat?                                             | 1 Yes
2 No
77 Do not know |  |
| 
If no report of a new cough or worsening of a chronic cough, please thank patient for their time and let them know that they do not need to take nasal self-swabs this week. Go to end of survey.
                              |                                                          |                                 |  |
| 8                                                                                                                                                                                                                                            | Did you already collect nasal swabs for the new illness? | 1 Yes
2 No
77 Do not know |  |
|                                                                                                                                                                                                                                              |                                                          |                                 |  |
|                                                                                                                                                                                                                                              |                                                          |                                 |  |
|                                                                                                                                                                                                                                              |                                                          |                                 |  |
|                                                                                                                                                                                                                                              |                                                          |                                 |  |
|                                                                                                                                                                                                                                              |                                                          |                                 |  |
| 
If the participant reports a new cough or a worsening of a chronic cough and hasn't already taken a swab, schedule an appointment to collect nasal self-swabs as soon as possible. Fill out an ARI/SARI episode Questionnaire.
 |                                                          |                                 |  |

